## Abstract

**Background:**

Severe acute respiratory syndrome coronavirus 2 will coexist with humans for a long time, and it is therefore important to develop effective treatments for coronavirus disease 2019 (COVID-19). Recent studies have demonstrated that antiviral therapy is a key factor in preventing patients from progressing to severe disease, even death. Effective and affordable antiviral medications are essential for disease treatment and are urgently needed. Azvudine, a nucleoside analogue, is a potential low-cost candidate with few drug interactions. However, validation of high-quality clinical studies is still limited.

**Methods:**

This is a multicentre, randomized, double-blind, placebo-controlled phase III clinical trial involving 1096 adult patients with mild-to-moderate symptoms of COVID-19 who are at high risk for progression to severe COVID-19. Patients will be randomized to (1) receive azvudine tablets 5 mg daily for a maximum of 7 days or (2) receive placebo five tablets daily. All participants will be permitted to use a standard treatment strategy except antiviral therapy beyond the investigational medications. The primary outcome will be the ratio of COVID-19-related critical illness and all-cause mortality among the two groups within 28 days.

**Discussion:**

The purpose of this clinical trial is to determine whether azvudine can prevent patients at risk of severe disease from progressing to critical illness and death, and the results will identify whether azvudine is an effective and affordable antiviral treatment option for COVID-19.

**Trial registration:**

ClinicalTrials.gov NCT05689034. Registered on 18 January 2023.

**Supplementary Information:**

The online version contains supplementary material available at 10.1186/s13063-024-07914-3.

## Introduction

### Background and rationale {6a}

Since December 2019, coronavirus disease 2019 (COVID-19) caused by severe acute respiratory syndrome coronavirus 2 (SARS-CoV-2) has become a global pandemic. By Nov 8, 2023, according to data from the World Health Organization (WHO), 771,820,937 cases of COVID-19 had been confirmed globally, and 6,978,175 of the patients had died (http://covid19.who.int) [1]. The disease continues to spread globally and has become a major threat to human health, bringing an enormous socioeconomic burden to individuals, families, and society [2]. Multiple society guidelines recommend that COVID-19 patients be treated with antiviral medication, corticosteroids, and biological agents according to the disease severity and clinical manifestations [3, 4]. Among these treatments, antiviral therapy is a key factor in preventing patients from progressing to severe disease, viral sepsis, and even death. 3-Chymotrypsin-like cysteine protease enzyme inhibitors (such as nirmatrelvir-ritonavir, known as Paxlovid) have been proven to be effective in reducing mortality in patients with a risk of disease progression to severe COVID-19 in both double-blind, randomized, controlled studies and the real world [5, 6]. In addition, RNA-dependent RNA polymerase (RdRp) nucleoside analogues, such as molnupiravir and remdesivir, have also showed evidence of accelerating SARS-CoV-2 RNA clearance or reducing hospitalization or death in COVID-19 patients [7–10]. If applied early, the viral load can decline over time, thus reducing the physiological damage directly caused by coronavirus and mitigating the inflammatory storm [11, 12]. Due to the high cost of the antiviral medications available on the market, effective and more affordable medications are still essential for disease treatment and are urgently needed.

SARS-CoV-2 is a new type of RNA virus. Azvudine is an RdRps nucleoside analogue given as 5 mg once daily for up to 14 days that has gained emergency approval for treatment of COVID-19 patients in the diagnosis and treatment protocol for COVID-19 in China (trial version 9) since August 2022 [13, 14]. However, the drug has not been validated by high-quality clinical studies. Compared with Paxlovid, a widely used anti-COVID-19 drug combination, azvudine is advantageous because of its lower price and fewer drug interactions. Quite a few retrospective studies have also found a decreased mortality among users of azvudine [15–17]. Shen et al. reported that azvudine could reduce mortality in COVID-19 patients (*HR*: 0.26; 95% *CI*: 0.07–0.94), by comparing 226 COVID-19 patients treated with azvudine with 226 matched controls. Another study conducted by Zong et al. showed that azvudine was associated with reduced in-hospital mortality through propensity score matching and univariate analysis (*OR* 0.38, 95% *CI* 0.23–0.62). A multicentre study including 1110 hospitalized patients also demonstrated the effectiveness of azvudine in reducing mortality in COVID-19 patients by multivariate analysis and inverse probability weighting (*OR* 0.75, 95% *CI* 0.61–0.93). However, well-designed, large-scale randomized trials focusing on critical illness and hospitalization prevention are lacking.

This multicentre, randomized, double-blind, placebo-controlled, phase III study aimed to determine whether azvudine can prevent patients with mild-to-moderate symptoms of COVID-19 at risk of severe disease from progressing to critical illness and death.

### Objectives {7}

The objectives of this trial were to assess the efficacy and safety of azvudine for COVID-19 patients with risk factors for progressing to critical illness. We hypothesized that azvudine would be an effective and safe antiviral drug for COVID-19 patients.

### Trial design {8}

This is a prospective multicentre, placebo-controlled, randomized, double-blind phase III trial, with a superiority design. A total of 1096 symptomatic adult patients with COVID-19 infection who are at increased risk of progressing to critical illness, based on their demographics and comorbidities, will be recruited from January 2023 through January 2024 [5]. The patients will be randomized at a 1:1 ratio to the treatment group and placebo group and treated with azvudine and placebo, respectively (Additional file 1). The investigator will observe and record subjects’ disease progression or remission and adverse drug reactions and analyse the data. Double blinding will be used in the trial.

This protocol was designed according to the Standard Protocol Items: Recommendations for Interventional Trials (SPIRIT) 2013 Statement (Additional file 2) [18] and registered at ClinicalTrials.gov (ID: NCT05689034).

## Methods: participants, interventions, and outcomes

### Study setting {9}

The Peking Union Medical College Hospital (PUMCH) is the initiator and responsible for this programme. Several hospitals in China participate as subcentres for patient recruitment, diagnosis and treatment, and data collection. The subcentres are listed in the China Human Genetic Resources Service System (https://apply.hgrg.net) and the Medical Research Registration and Filing Information System (https://www.medicalresearch.org.cn/login).

### Eligibility criteria {10}

#### Inclusion criteria

Age of 18 years or older (inclusive)No more than 5 days since symptom onset and a positive result of nucleic acid and/or antigen test for COVID-19 within 5 days before enrolmentThe presence of at least one symptom related to COVID-19 infection at the time of enrolment (Table 1)

**Table 1 Tab1:** Subject’s symptom recording form

**Symptoms**	D1	D2	D3	D4	D5	D6	D7	……	D14	D28
Cough, sputum										
Sore throat										
Stuffy nose										
Running nose, sneezing										
Decreased sense of smell										
Decreased sense of taste										
Dyspnoea										
Headache										
Fever, chills										
Highest temperature of the day										
NSAIDs or not										
Muscle or joint pain										
Fatigue										
Nausea										
Vomiting										
Diarrhoea										
Adverse events										Consent to use effective pregnancy control measures for females of child-bearing age and a negative urine pregnancy testThe presence of at least one of the following characteristics associated with an increased risk of developing severe illness:Age ≥ 65 yearsBody mass index > 30 kg/m.^2^Current smokers (still smoking within 30 days before enrolment and smoking at least 100 cigarettes in total) [5]Status of immunosuppression, including but not limited to the following:Haematopoietic stem cell transplantation or solid organ transplantationPrimary immunodeficiency diseaseProlonged use of corticosteroids (≥ 20 mg/day for at least 14 days in the case of prednisone within the last 30 days)Use of biologic agents (such as infliximab)Use of immune-modulators (including but not limited to methotrexate, azathioprine)Chemotherapy and/or radiation therapy for any malignancies within 90 days (for chest radiation therapy, the time interval should be more than 6 months).Chronic lung disease (asthma under treatment, bronchiectasis, chronic obstructive pulmonary disease, pulmonary hypertension, obstructive sleep apnoea syndrome, interstitial lung disease, etc.)HypertensionCardiovascular and cerebrovascular diseases (myocardial infarction, stroke, transient ischaemic attack, heart failure, angina pectoris requiring nitrate therapy, coronary artery bypass grafting, post-percutaneous coronary intervention, post carotid endarterectomy, and aortic bypass surgery, etc.)Type 1 or type 2 diabetesNeurodevelopmental abnormalities (such as cerebral palsy, Down’s syndrome) or other genetic or metabolic syndromes and severe congenital malformationsActive tumours (excluding localized skin cancer)No vaccination against COVID-19

### Exclusion criteria

Known or suspected allergy to the components of azvudine tabletsPatients diagnosed with severe or critical COVID-19 infection on screeningPatients with severe liver disease (total bilirubin ≥ 2 × upper limit of normal [ULN], alanine aminotransferase [ALT], and aspartate aminotransferase [AST] ≥ 3 × ULN)Patients with severe renal insufficiency (glomerular filtration rate ≤ 60 mL/min/1.73 m^2^) or currently on continuous renal replacement therapy, haemodialysis, and/or peritoneal dialysisPatients with malabsorption syndrome or any other condition compromising gastrointestinal absorption or patients requiring parenteral nutrition or with difficulty taking the investigational product orallyPatients with known HIV infectionPatients with diabetic ketosis or a hyperosmolar hyperglycaemic statePatients with a total neutrophil count < 750 cells/LPregnant or lactating women or those who plan to have a child during participation in this study and within 6 months after the end of this studyPatients currently participating in another interventional clinical trial or who are currently using another investigational productPatients with other uncontrolled active infections (must be aetiologically confirmed) in addition to COVID-19 infectionThe presence of any comorbidities requiring hospitalization and/or a surgical procedure within 7 days prior to the start of this study or a comorbidity considered life-threatening within 30 days prior to the start of this study, as determined by the investigatorPatients who have received or are expected to receive convalescent plasma for COVID-19Patients previously treated with antiviral agents that have been proven to be effective against COVID-19, including but not limited to nirmatrelvir/ritonavir or molnupiravirPatients with other conditions that make it inappropriate for the participant to take part in this trial at the investigator’s discretion

The risk factors for critical infection described in the inclusion criteria and the adverse drug reactions and patient comorbidities that may affect clinical outcomes described in the exclusion criteria were derived from reported studies [19, 20].

### Who will take informed consent? {26a}

The informed consent will be obtained from COVID-19 patients who meet all inclusion criteria and does not meet any exclusion criteria.

Before being enrolled in the trial, a researcher who has received training will provide patients and their families with an introduction to the study’s purpose and content. The potential benefits and risks will also be explained to them. A 24-h timeframe will be given to the patients and their families to decide whether to participate in the trial, ensuring that their participation is completely voluntary. Additionally, it will be clarified to the patients that their decision to participate or not will have no impact on their regular treatment. Any identifying information, such as names and hospital numbers, will be encoded to maintain confidentiality. The personal information of all participants will always be kept private.

### Additional consent provisions for collection and use of participant data and biological specimens {26b}

Not applicable. No data and specimens will be used for other studies.

## Interventions

### Explanation for the choice of comparators {6b}

This is a prospective placebo-controlled, randomized, double-blind phase III trial. The comparator is placebo five tablets once daily for 7 days. The placebos are manufactured and packaged through the same process as the study drug and are produced by the same manufacturer and product line. The placebo formulation provided has the same physical appearance as the active formulation, contains the same inactive ingredients, and will be used in the study for masking purposes.

### Criteria for discontinuing or modifying allocated interventions {11b}

#### Participants will withdraw from the study for any of the following reasons:

Participants with poor compliance who cannot cooperate with the clinical examination and follow-up.Patients who voluntarily quit this clinical trial.

#### Patients will be advised to discontinue medication under the following conditions:

The illness of the subject worsens, and the researcher determines that the benefit of the subject is poor and the subject is unwilling to continue receiving trial drug treatment.The subject has experienced serious adverse events (SAEs) related to the investigational drug (definitely related, likely related, possibly related), and the researcher has determined that it is not suitable to continue participating in this trial.Other conditions occur for which the researcher believes that the subject is not suitable to continue receiving investigational drug. Serious unexpected suspected adverse reactions must be reported and documented according to the appropriate requirements of the research centre’s institutional or ethics committee.

### Strategies to improve adherence to interventions {11c}

The clinical research coordinator will determine if subjects are recording their condition daily by checking the subject’s symptom recording form (Table 1) and reminding each subject to take their medication daily. Upon completion of their medication, all subjects will be expected to return the medication package upon request.

### Relevant concomitant care permitted or prohibited during the trial {11d}

Relevant concomitant care was shown in Table 2.

### Provisions for posttrial care {30}

During outpatient treatment or after discharge from the hospital, study subjects should follow the following instructions and abide by the precautions specified by the research centre: continue rehabilitation for 3 to 6 weeks, wear a mask if necessary, maintain hand hygiene and do not share personal belongings, pay special attention to avoiding contact with high-risk groups, and report immediately to the principal investigator or his or her team in the event of fever and/or respiratory symptoms.

All subjects will be followed up for the disease through monitoring, consultations, and examinations that will benefit the patient’s treatment and recovery. If the patient’s condition warrants, additional outpatient consultation or hospitalization will be arranged for the subject in addition to routine visits.

### Outcomes {12}

The primary outcome of this trial is the ratio of COVID-19-related critical illness and all-cause mortality among the two groups within 28 days. COVID-19-related critical illness is defined as a patient who requires mechanical ventilation or extracorporeal membrane oxygenation or a patient maintaining oxygen saturation (SpO_2_) above 90% who requires high-flow oxygen inhalation with a fraction of inspired oxygen (FiO_2_) not less than 60% or requires noninvasive ventilation with a FiO_2_ not less than 60%.

The secondary outcomes are as follows: (1) COVID-19 viral load measured from pharyngeal swabs at the D1, D3, D7, and D14 timepoints, (2) incidence of azvudine-related adverse events (AEs) and serious adverse events, (3) duration of COVID-19-related symptoms, (4) all-cause mortality within 6 months, (5) days of hospitalization and intensive care unit stay, and (6) the ratio of COVID-19-related severe illness defined on the China Formula of Diagnosis and Treatment for COVID-19 (trial version 10). In detail are as follows: (1) shortness of breath with respiratory rate ≥ 30 breaths/min, (2) SpO_2_ ≤ 93% when inhaling air at rest, (3) partial pressure of arterial oxygen/FiO_2_ ≤ 300 mmHg, and (4) progressive worsening of clinical symptoms and obvious lesion progression > 50% on chest imaging within 24 to 48 h.

The safety endpoints consist of adverse events that emerge during or after the treatment period and subsequent observation period until 28 days. SAEs and AEs leading to discontinuation of the trial drug or placebo will be coded according to the definition of severe adverse events published by the FDA (https://www.fda.gov/safety/reporting-serious-problems-fda/what-serious-adverse-event).

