### Sample size {14}

This study aims to determine the efficacy of a new antiviral compared to placebo in reducing critical illness or all-cause mortality on day 28 in COVID-19 patients.

The sample size was calculated based on the superiority test. The primary endpoints are the disease critical rate and mortality rate. Based on the data reported in Hong Kong for patients with COVID-19 from the end of 2020 to March 2022, the number of deaths and serious illnesses was 6866 and 8875, respectively [21]. Previous data on another antiviral drug, Paxlovid, showed that the placebo group had 65 hospitalizations and 12 deaths, while the Paxlovid group had no deaths and 8 hospitalizations [5]. Combined with data from Hong Kong, it was speculated that there may be 15–16 severe patients in the placebo group and 2 severe patients in the Paxlovid group. Therefore, the disease critical rate and mortality rate in other countries and China are assumed to be 2.6% in the standard treatment group and can be reduced to 0.19% with effective treatment. With a power of 90% (1 sided *α* = 0.025 and *β* = 0.10), a sample size of 986 patients in each group is needed. The sample size calculations were performed using SAS software, version 9.4 (SAS Institute Inc., USA).

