## Statistical methods

### Statistical methods for primary and secondary outcomes {20a}

All data will be analysed using SAS software, version 9.4 (SAS Institute Inc., USA). A two-tailed *p* < 0.05 will be considered statistically significant in all statistical tests (except for the main efficacy indicators and other specified instructions).

The full analysis set (FAS), modified intention-to-treat set (mITT), per-protocol set (PPS), and safety set (SS) will be divided for analysis. FAS includes all eligible and randomized patients. PPS includes eligible patients with better compliance (80–120%), and completing necessary items of CRF.SS includes all patients enrolled in the study who have received at least one dose of medication and have at least one safety evaluation. Baseline characteristics analysis will be based on FAS, efficacy analysis will be based on FAS and PPS, and safety analysis will be based on SS. Unblinded patients will be excluded from PPS.

Continuous data will be summarized as the mean ± standard deviation, median, minimum, maximum, lower quartile, and upper quartile. Categorical data will be presented and summarized as frequencies and percentages in each category.

Between-group comparisons will be conducted by using paired *t*-tests or Wilcoxon rank tests for continuous data, chi-square tests or Fisher exact tests for categorical data, Wilcoxon rank tests or CMH tests for ranked data, and Kaplan‒Meier estimates for time-to-event data. The principles of intention-to-treat analysis will be used.

Efficacy analysis will be based on FAS and PPS. The primary efficacy endpoints are COVID-19-related critical illness and all-cause mortality within 28 days (whichever happens first), which will be analysed based on a time-to-event manner. Kaplan‒Meier method will be used to describe the incidence rates of the primary endpoint in each group separately at 28 days. Between-group comparisons will be performed by the log rank test. A Cox regression model will be used to estimate the hazard ratio and corresponding 95% confidence interval and adjust for potential covariates such as centres. Secondary efficacy endpoint analysis will be performed according to general statistical considerations. The specifics of these methods will be thoroughly outlined in the statistical analysis plan.

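### The primary endpoint makes SpO2 above 90% a condition for counting patients on high-flow oxygen or noninvasive ventilation, where the target of that support was probably meant

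*Protocol article*

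**What the plan says.** The protocol article defines COVID-19-related critical illness once, under Outcomes {12}, and no other section restates it. The definition has two limbs.

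- **First limb:** "a patient who requires mechanical ventilation or extracorporeal membrane oxygenation". It carries no SpO2 condition.
- **Second limb:** "a patient maintaining oxygen saturation (SpO_2_) above 90% who requires high-flow oxygen inhalation" at an FiO2 of 60% or more, "or requires noninvasive ventilation with a FiO_2_ not less than 60" per cent.

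Statistical methods {20a} analyses the composite as time to first event: "COVID-19-related critical illness and all-cause mortality within 28 days (whichever happens first", by Kaplan–Meier, log-rank test and Cox model. Under Data collection {18a}, inpatients are followed daily until a primary event or discharge. Recruitment {15} names 46 sites in 17 provinces.

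The same Outcomes section also defines severe illness, a secondary outcome. There a low saturation marks the worse state: "SpO_2_ ≤ 93% when inhaling air at rest".

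**The concern.** In the second limb the saturation phrase describes the patient who is counted. It is not attached to the support as its purpose. Taken at its word, the definition turns the severity order round at 90%: of two patients on the same high-flow oxygen at the same FiO2, the better-oxygenated one is an event and the other is not.

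This is the primary endpoint. One site may apply the literal text and another the probable meaning, and they would then classify the same patient in opposite ways. Under the literal text some events are dated later than the deterioration they represent, and a few may not be recorded at all. The trial expects very few events, so little misclassification is needed to be noticeable.

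**Working it through.** **1. Which patients the wording affects.** The table sets the literal text against the probable meaning, in which the support is needed to keep SpO2 above 90%.

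| Patient, by day 28 | Literal text | Probable meaning |
|---|---|---|
| High-flow oxygen, FiO2 ≥ 60%, SpO2 above 90% | Event | Event |
| Same support, SpO2 at or below 90%, later above 90% on that support | Event, dated later | Event at start of support |
| Same support, SpO2 at or below 90%, later mechanical ventilation, ECMO or death | Event, dated later | Event at start of support |
| Same support, SpO2 never above 90% on it, no ventilation or ECMO, alive at day 28 | Not an event | Event |

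Only the last row is a permanent loss. The two middle rows are delays. The definition fixes no time or duration for the SpO2 reading, so a later value above 90% satisfies even the literal text.

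**2. Noninvasive ventilation.** The second "requires" shares its subject with the first, so the SpO2 condition most naturally covers noninvasive ventilation too, although the clause could be read as standing alone. The first limb adds a further doubt. If mechanical ventilation there included noninvasive ventilation, any such patient would already count at any FiO2, and the noninvasive clause of the second limb would be redundant. That favours an invasive-only reading, but the text does not say so.

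**3. How many events there are to lose.** The inputs come from Sample size {14}: rates "assumed to be 2.6% in the standard treatment group and can be reduced to 0.19% with effective treatment", and "With a power of 90% (1 sided *α* = 0.025 and *β* = 0.10". The unpooled two-proportion formula gives

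n per arm = (1.960 + 1.282)² × (0.026 × 0.974 + 0.0019 × 0.9981) / (0.026 − 0.0019)² = 10.51 × 0.02722 / 0.000581 ≈ 492.4, so 493 per arm and 986 in total.

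This reproduces the plan's number as a total. The section says "a sample size of 986 patients in each group is needed", which is a separate labelling matter. Dividing 986 by 0.90 for dropout gives 1096, as stated in Recruitment {15}.

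Expected events with 493 per arm:
- placebo: 493 × 0.026 = 12.8
- azvudine: 493 × 0.0019 = 0.9
- total: 13.7, about 14

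One event is therefore about 1/13.7 = 7% of the expected total.

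**4. What a delay does.** With so few events the numbers at risk barely change through the 28 days. Ignoring dropout, they go from 493 and 493 to about 480.2 and 492.1. The placebo share of those at risk moves only from 0.500 to 480.2 / 972.3 = 0.494. An event dated later, but still within 28 days, therefore alters the log-rank statistic very little. What costs information is an event that falls outside the window, is never recorded, or is classified differently from site to site.

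**The case against.** The strongest reply is that this is a slip of expression. The words for maintaining saturation stand next to the words for requiring support, and a clinician would probably read them as support needed to maintain saturation. The article condenses protocol version 1.5, and neither that document nor the eCRF is shown, so the wording that sites use may be sound. This stands as far as intent goes. It does not repair the stated definition, which gives a different answer if followed.

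A reader might infer three stronger things that the documents do not support.

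- **That the sickest patients are dropped from the endpoint.** Most routes out of that state lead back in: ventilation, ECMO, death, or recovery above 90% on the same support. Only the last row of the table is lost.
- **That power falls by a stated amount.** If 0%, 10%, 20% or 30% of events were lost equally in both arms, power with 493 per arm would be 89.8%, 86.5%, 82.3% or 76.9% by the pooled formula. Exact calculation gives 95.1%, 92.7%, 89.3% or 84.7% for chi-square and 91.7%, 87.7%, 82.0% or 74.0% for Fisher. Nothing in the documents supports any of these loss fractions. The calculation ignores the events regained, and these are not the planned log-rank test. The 2.6% rate was also derived from outside data on deaths, serious illness and hospitalisations, not from this FiO2 and SpO2 definition.
- **That the comparison is biased.** Patients and researchers are blinded under {17a}, so inconsistent classification should not differ by arm.

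**Conclusion.** The definition is wrong as written and should be corrected. Read literally, it withholds an event from a patient on high-flow oxygen at an FiO2 of 60% or more, and on the natural reading from one on noninvasive ventilation, for as long as SpO2 is at or below 90%. It grants the event to a better-oxygenated patient on the same support.

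The likely consequence is delayed event dates and uneven classification across 46 sites. Permanent loss is limited to survivors who, by day 28, are never ventilated, never receive ECMO and never exceed 90% on that support. Their number is unknown and may be small. With about 14 events expected, each weighs about 7% of the total, which is reason enough to remove the ambiguity. It is not a basis for quoting a power loss.

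The conclusion rests on the article's wording being the operative one and, for the event count, on the planning rates with 493 evaluable patients per arm.

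**What to change.** Reword the second limb of the outcome definition, for example: *requires high-flow oxygen or noninvasive ventilation, either with FiO2 not less than 60%, to maintain SpO2 above 90%, whether or not that level is reached*. State that mechanical ventilation in the first limb means invasive ventilation, if that is intended. Put the same wording in the eCRF and its completion notes, and do so before unblinding.

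The cost is one sentence and an eCRF note. No new measurement should be needed, assuming the type of support and FiO2 are already recorded, as the present definition requires. If cases have already been classified under the current text, re-read them blind to allocation. The change touches the outcome definition only and alters no treatment rule.
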